### Sample size calculation

The sample size calculation is based on the proportion of patients with treatment success at 6-month follow-up (primary endpoint). An absolute difference in success rate of 30%, with success rates of 35 and 5% for SNM and PCT respectively, is considered clinically relevant. The sample size required to detect this difference with a two-sided Fisher’s exact test equals 64 patients in total (alpha 0.05, power of 80 and 5% drop-out rate). With a randomization ratio of 3:2, 38 patients will be randomized to SNM and 26 patients will be randomized to PCT.

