### Statistical analysis

All statistical analyses will be conducted according to the intention-to-treat principle using SPSS (SPSS, Inc., Chicago, IL, USA). Drop-outs will be classified as failures and missing values will be imputed using multiple imputation stochastic regression imputation. Values to impute will be drawn using predictive mean matching. *P* values of 0.05 and lower will be considered to indicate statistical significance. The number of patients with treatment success will be displayed by frequencies and percentages. Logistic regression, adjusted for the effect of possible unbalanced distributions of baseline characteristics, will be used to assess the difference in proportions of patients treated successfully at 6 months between the SNM and PCT group. Multivariable linear mixed-effect models corrected for covariates at baseline will be used to analyze differences in trends of the average DF a week between the SNM and the PCT group.

For the secondary outcome parameters, dichotomous parameters will be displayed using frequencies and percentages. Differences in proportions between the SNM and PCT group will be analyzed by means of logistic regressions, adjusted for the effect of possible unbalance of baseline characteristics. Continuous parameters will be presented as mean and standard deviation if distributed normally and as median and quartiles if not normally distributed, as judged using histograms. The difference in scores between the SNM and PCT group at 6 months will be analyzed by means of linear regression, adjusted for the effect of possible unbalanced distributions of baseline characteristics. No statistical analysis will be conducted on the adverse events and complications.

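### The trial is sized on Fisher's exact test but analysed by logistic regression with no provision for sparse events; at the planning rates the primary odds ratio is not finite in about one trial in four

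*Protocol article*

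**What the plan says.** The Sample size calculation section of the protocol article takes 6-month treatment success as its basis: "The sample size calculation is based on the proportion of patients with treatment success at 6-month follow-up (primary endpoint". The planning effect is a 30-point difference, "with success rates of 35 and 5% for SNM and PCT respectively, is considered clinically relevant". The calculation is for Fisher's test, two-sided, and its result is given in these words: "exact test equals 64 patients in total (alpha 0.05, power of 80 and 5% drop-out rate". On allocation it states: "With a randomization ratio of 3:2, 38 patients will be randomized to SNM and 26 patients will be randomized to PCT".

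The Statistical analysis section analyses the same endpoint differently. There a logistic regression, with adjustment for baseline imbalance, "will be used to assess the difference in proportions of patients treated successfully at 6 months between the SNM and PCT group". The software is SPSS. Fisher's test is not mentioned there. The section does not say whether the p-value is Wald or likelihood-ratio, and it names no exact or penalised method. On incomplete data it states: "Drop-outs will be classified as failures and missing values will be imputed using multiple imputation stochastic regression imputation".

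**The concern.** Sizing on one test and analysing with another is often harmless, because with moderate event counts the usual tests for a 2×2 table nearly agree. Here they need not, because the plan expects about one success in the control arm. If no PCT patient succeeds, the likelihood keeps rising as the treatment coefficient grows. Ordinary logistic regression then has no finite odds ratio, and the Wald statistic collapses because the standard error grows faster than the coefficient. Baseline covariates do not cure this: every PCT outcome is still a failure.

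The results affected are those in which SNM looks best. The article says they will inform a final national reimbursement decision, so a clear benefit could appear as a primary effect that cannot be estimated or, with the Wald p-value, as a non-significant one.

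**Working it through.** **Inputs** (Sample size calculation section): success 0.35 with SNM and 0.05 with PCT; 38 and 26 patients; two-sided alpha 0.05; 5% drop-out. The Statistical analysis section counts drop-outs as failures. Applying 5% to each arm is my assumption.

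**1. Reproducing the plan's figure.** Power is the sum, over all pairs (a, b) of SNM and PCT successes, of Bin(a; n1, 0.35) × Bin(b; n2, 0.05) where p ≤ 0.05. For two-sided Fisher, 34 + 23 = 57 patients give 77.7% and 36 + 24 = 60 give 81.0%. Then 60 / 0.95 = 63.2, rounded up to 64. The stated sample size reproduces.

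**2. Chance of a zero cell.**
- Expected PCT successes: 26 × 0.05 = 1.3.
- P(no PCT success) = 0.95^26 = 0.2635, about 26%.
- With drop-outs as failures the PCT rate is 0.05 × 0.95 = 0.0475, and 0.9525^26 = 0.282, about 28%.

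In all these trials the maximum-likelihood odds ratio is not finite. Fisher's test is significant in nearly all of them: 0.2615 of the 0.2635.

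**3. Two example tables.**
- 13/38 against 0/26: Fisher p = 0.0004. An ordinary logistic fit gave coefficient 20.9, standard error 5733 and Wald p = 0.997.
- 9/38 against 1/26: the odds ratio is (9 × 25)/(1 × 29) = 7.76, with log 2.049. The standard error is √(1/9 + 1/29 + 1/1 + 1/25) = 1.089, so z = 1.88 and Wald p = 0.060. Fisher p = 0.039.

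**4. Power and type I error at 38/26**, by the same enumeration without covariates. A zero cell counts as non-significant for Wald. For Firth, the penalised likelihood of the two-group model is maximised at (x + 0.5)/(n + 1) in each arm, and at (a + b + 1)/(n1 + n2 + 2) when the arms are equal; twice the difference is referred to chi-square on 1 df.

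| Test | Power, 35% v 5% | Power, drop-outs as failures (33.25% v 4.75%) | Type I error at common rate 5% / 10% / 20% |
|---|---|---|---|
| Fisher, two-sided | 84.5% | 81.6% | 0.9% / 2.3% / 3.2% |
| Logistic, Wald | 57.0% | 51.6% | 0.05% / 0.65% / 3.4% |
| Logistic, likelihood ratio | 90.3% | 88.6% | 5.5% / 6.9% / 6.2% |
| Firth, penalised likelihood ratio | 87.4% | 84.8% | 2.6% / 4.1% / 5.2% |

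The Wald test cannot exceed 1 − 0.2635 = 73.65% power here. Given at least one PCT success its power is 0.5696 / 0.7365 = 77%.

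**5. Effect of adjustment.** In 4,000 simulated trials with three covariates that have no effect, Wald power was 56.8% and likelihood-ratio power 89.6%. Adjustment hardly changes the picture.

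**The case against.** A reader might infer that the trial has 57% power and that the stated 80% is wrong. The article does not support that. It attributes 80% to Fisher's test, where it reproduces. It says logistic regression and never says Wald. A likelihood-ratio test from the same model has about 90% power. Wald is a likely reading, because pooling coefficients and standard errors after multiple imputation leads to a Wald-type test, but it remains an inference.

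It can also be said that the choice of p-value and a fallback for separation belong in an analysis plan that is not shown. For the p-value that is fair. It does not answer the estimation problem: the article itself names the primary method, and under ordinary maximum likelihood that method has no finite odds ratio in a quarter of trials at the article's own rates, whichever p-value is taken.

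The Wald deficit is also specific to a PCT rate near 5%. For the same 30-point difference at 40% against 10%, Wald has 71.5% power and Fisher 75.5%; at 45% against 15%, Wald has 71.5% and Fisher 68.3%. This is true, but 5% is the rate on which the plan rests.

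Successes will also be shown as counts and percentages, so 13/38 against 0/26 would not be hidden. That limits the harm but supplies no primary estimate or test.

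Finally, one could fault logistic regression for giving an odds ratio when the target is an absolute difference. That is a preference. Percentages are reported by arm, and the cost per successfully treated patient is a separate bootstrapped analysis.

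**Conclusion.** The point holds in a limited form. The sizing test and the primary analysis do not match. With 35% and 5% success and 38/26 patients, the planned odds ratio is not finite under ordinary maximum likelihood in about 26% of trials, or 28% with 5% drop-out per arm counted as failures.

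The consequence for power is conditional. It is about 57% (52% with those drop-outs) if the Wald p-value is used, and about 90% (89%) with the likelihood-ratio test, which somewhat exceeds the nominal 5%. A range that wide should not rest on a choice that could still be made after the data are seen. No stated figure is shown to be wrong: 64 patients and 80% power stand for Fisher's test. A fuller analysis plan may already settle the matter, in which case the article's wording only needs aligning with it.

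**What to change.** In the Statistical analysis section, name a primary method that works when one arm has no successes. Either of these would do:
- Firth-penalised logistic regression with a profile-likelihood test and confidence interval, adjusted for the minimisation factors (study site, age, gender).
- Two-sided Fisher's exact test as the confirmatory test, with the Firth estimate as the adjusted effect.

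Then make the Sample size calculation section refer to the same test. Simulation with adjustment for site, age and sex (3,000 trials) put Firth at about 87% power with type I error of 1.8% to 4.6%, so 64 patients remain enough at the planning rates.

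The cost is about a paragraph of wording, with no extra patients or data. Firth regression needs an add-on or another package. Fisher's test is conservative and unadjusted. Either choice needs a rule for combining results across imputed data sets.

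Only if Wald logistic regression is kept should the power in the Abstract and the Sample size calculation section be restated as about 57%. On the same enumeration, Wald would need about 54 + 36 = 90 evaluable patients to reach 80%.

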### Economic evaluation

The economic evaluation consists of a trial-based economic evaluation (TBEE) and a model-based economic evaluation (MBEE). The TBEE will consist of a cost-utility analysis (CUA) and a cost-effectiveness analysis (CEA), both with a time horizon of 6 months. The incremental cost-effectiveness ratio (ICER) for the CUA is incremental costs per quality adjusted life year (QALY) conducted from a societal perspective. The ICER for the CEA is incremental costs per successfully treated patient (based on the primary outcome) conducted from a health care perspective. With a time horizon of 6 months, no discounting will be applied.

The cost analysis for the societal perspective consists of health care costs, patient and family costs, and costs outside the health care sector will be taken into account. For the health care perspective, only health care costs will be taken into account. Health care costs in the SNM group will be the costs of the device, costs of implantation, costs of complications, costs of follow-up visits, and costs due to lack or loss of efficacy (including costs of PCT). In the control group, the costs of PCT will consist of costs of laxatives, colonic irrigation, follow-up visits, hospital admissions, etc. Patient and family costs in both groups will be out-of-pocket expenses (e.g., over-the-counter medication) and travel costs. Costs outside the health care sector will consist of productivity losses (of adult patients and parents of adolescents) and school/study absence (if applicable).

Health care costs will be valued with reference pricing [42]. If reference prices are not available, prices will be estimated using the (financial) registry of the hospital. Productivity losses will be valued using the friction cost method and informal care by using the proxy good method corresponding to the Dutch guidelines for economic evaluations and the manual for costing research [42, 43]. Out-of-pocket expenses will be valued using market prices derived from the tailored cost-questionnaire. Absenteeism at school (i.e., repeating classes, school drop-out) will be valued using the Dutch guidelines for intersectoral costs and benefits [44].

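### The primary model is a logistic regression, but the plan gives no step from it to the absolute difference in success, with a confidence interval, on which clinical relevance and the cost-effectiveness ratio are expressed

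*Protocol article*

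**What the plan says.** The Sample size calculation section of the protocol article sets the target on the absolute scale: "An absolute difference in success rate of 30%, with success rates of 35 and 5% for SNM and PCT respectively, is considered clinically relevant". It sizes the trial with a two-sided Fisher's exact test, and the requirement "equals 64 patients in total (alpha 0.05, power of 80 and 5% drop-out rate"). On allocation it states: "With a randomization ratio of 3:2, 38 patients will be randomized to SNM and 26 patients will be randomized to PCT".

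The Statistical analysis section displays success as counts and percentages and takes P values up to 0.05 as significant. It then names the primary model, a logistic regression with adjustment for baseline imbalance, which "will be used to assess the difference in proportions of patients treated successfully at 6 months between the SNM and PCT group". Differences in proportions for the dichotomous secondary outcomes are also assigned to adjusted logistic regression. These outcomes are a 50% reduction in defecations with straining and a 50% reduction in defecations with a sense of incomplete evacuation. The section names neither an odds ratio, nor a risk difference, nor a confidence interval.

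The Economic evaluation section states: "The ICER for the CEA is incremental costs per successfully treated patient", where success is that of the primary outcome. Its stochastic uncertainty is to be assessed by bootstrapping.

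**The concern.** The treatment coefficient of a logistic model is a log odds ratio. It is not a difference in proportions. It leads to one only through a further step, such as averaging predicted risks over the covariates under each treatment, and the article names no such step. The model is therefore fixed, but the quantity it is said to assess does not come out of it directly.

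The clinically relevant effect and the cost-effectiveness ratio are both on the absolute scale, and the results are meant to inform a reimbursement decision. The size of the absolute benefit and its uncertainty are what that decision needs. The low planned PCT success rate sharpens the point, because an odds ratio is least stable when one arm has very few events.

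**Working it through.** **Inputs.** From Sample size calculation: success 35% (SNM) and 5% (PCT), 38 and 26 patients, two-sided Fisher's exact test, alpha 0.05, power 80%, 5% drop-out. From Statistical analysis: drop-outs count as failures, so the denominators are kept at 38 and 26.

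**1. The plan's own figure.** Summing Fisher rejections over both binomial distributions gives power 0.810 with 36 + 24 = 60 evaluable patients. Then 60/0.95 = 63.2, which rounds up to 64. The stated total is reproduced. With all 38 + 26 analysed, power is 0.845.

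**2. Odds ratio at the planning rates.** (0.35/0.65)/(0.05/0.95) = 10.2.

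**3. An odds ratio alone does not fix the absolute difference.** With PCT rate p0, the SNM rate is p1 = OR × p0/(1 − p0 + OR × p0). For OR = 10.2 (rates other than 5% are assumptions, used to show the range):

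| PCT rate | SNM rate | Difference (points) |
|---|---|---|
| 2% | 17.3% | 15 |
| 5% | 35.0% | 30 |
| 10% | 53.2% | 43 |

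Conversely, a 30-point difference is an odds ratio of 23 at a PCT rate of 2%, 10.2 at 5% and 6.0 at 10%.

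**4. A result close to plan: 13/38 against 1/26.**
- Crude odds ratio: (13/25)/(1/25) = 13.0. The standard error of its log is √(1/13 + 1/25 + 1/1 + 1/25) = 1.076. The 95% CI is exp(2.565 ± 1.96 × 1.076) = 1.6 to 107.
- Risk difference: 13/38 − 1/26 = 0.342 − 0.038 = 30.4 points. The Newcombe interval combines the two Wilson intervals (21.2% to 50.1%; 0.7% to 18.9%). Lower limit: 0.304 − √[(0.342 − 0.212)² + (0.189 − 0.038)²] = 0.105. Upper limit: 0.304 + √[(0.501 − 0.342)² + (0.038 − 0.007)²] = 0.466. The 95% CI is 10.5 to 46.6 points.

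**5. No PCT successes.** The expected number is 26 × 0.05 = 1.3, and the probability of none is 0.95^26 = 0.26. The maximum-likelihood odds ratio is then not finite. The risk difference for 13/38 against 0/26 is 34.2 points. The Wilson upper limit for 0/26 is 12.9%, so the Newcombe lower limit is 0.342 − √[(0.342 − 0.212)² + 0.129²] = 0.159, and the upper limit is 0.501. The 95% CI is 15.9 to 50.1 points.

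**The case against.** The strongest reply is that the article is silent here rather than wrong. It names no effect measure, and a fitted logistic model can give an adjusted risk difference by standardisation. The choice of summary measure and interval is often left to the full protocol or SAP, which are not shown. The percentages per arm give the crude difference, and they also give any reader of an odds ratio the control rate.

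Much of this stands, and it rules out several stronger readings that a reader might infer:
- *That the trial will deliver only an odds ratio and a P value, and never an absolute difference with an interval.* The text does not say so. The crude difference follows from the reported counts, and the bootstrap in the Economic evaluation covers uncertainty in incremental success.
- *That 30 points is a criterion the result must meet.* It is a design effect for a test of equality. At 38 and 26 patients, Fisher's test is already significant at 7/38 against 0/26 (18.4 points, P = 0.035, Newcombe 95% CI 2.6 to 33.4). Significance below the design effect is ordinary in a superiority trial and is no defect.
- *That the cost-effectiveness ratio will use a different, unadjusted effect.* The article does not say whether that effect is adjusted.

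What the reply does not remove is that the article fixes a model for a difference in proportions which does not directly give one. The model's own estimate has about a one-in-four chance of not being finite under the planning rates. The bootstrap is specified for cost-effectiveness uncertainty, not as the primary clinical estimate, and it is not tied to the adjusted model.

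**Conclusion.** The point holds as a gap between the named model and the scale on which the article expresses its effect. It applies to the primary outcome and to the two dichotomous secondary outcomes. For the primary outcome at the planning rates, the odds ratio would be very imprecise (95% CI 1.6 to 107 for 13/38 against 1/26), and it would not be finite with probability about 0.26. The risk difference has a usable interval in both cases.

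These figures assume 5% PCT success and all 38 and 26 patients in the denominators. The odds ratios in the example tables are crude, because the adjustment covariates are not fixed in the article. The planned test and the sample size are not in question. The change should be made because it is nearly free and the results serve a reimbursement decision.

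**What to change.** In the Statistical analysis section:
- Make the absolute difference in success at 6 months, with a 95% CI, the primary effect estimate. If unadjusted, use a score-type interval (Newcombe or Miettinen-Nurminen). If adjusted, standardise over the covariates of the logistic model and name in advance a fitting and interval method that copes with zero PCT successes, for example a penalised fit.
- Keep the odds ratio as a secondary figure.
- Do the same for the two dichotomous secondary outcomes.
- Use the 30 points as context for reading the interval, not as a pass/fail threshold.

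In the Economic evaluation section, state whether the cost-effectiveness ratio uses the same estimate of the difference in success.

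The sample size stays at 64 and no new data are needed. The cost is a few sentences and a little more analysis work.

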### Economic evaluation

The economic evaluation consists of a trial-based economic evaluation (TBEE) and a model-based economic evaluation (MBEE). The TBEE will consist of a cost-utility analysis (CUA) and a cost-effectiveness analysis (CEA), both with a time horizon of 6 months. The incremental cost-effectiveness ratio (ICER) for the CUA is incremental costs per quality adjusted life year (QALY) conducted from a societal perspective. The ICER for the CEA is incremental costs per successfully treated patient (based on the primary outcome) conducted from a health care perspective. With a time horizon of 6 months, no discounting will be applied.

The cost analysis for the societal perspective consists of health care costs, patient and family costs, and costs outside the health care sector will be taken into account. For the health care perspective, only health care costs will be taken into account. Health care costs in the SNM group will be the costs of the device, costs of implantation, costs of complications, costs of follow-up visits, and costs due to lack or loss of efficacy (including costs of PCT). In the control group, the costs of PCT will consist of costs of laxatives, colonic irrigation, follow-up visits, hospital admissions, etc. Patient and family costs in both groups will be out-of-pocket expenses (e.g., over-the-counter medication) and travel costs. Costs outside the health care sector will consist of productivity losses (of adult patients and parents of adolescents) and school/study absence (if applicable).

Health care costs will be valued with reference pricing [42]. If reference prices are not available, prices will be estimated using the (financial) registry of the hospital. Productivity losses will be valued using the friction cost method and informal care by using the proxy good method corresponding to the Dutch guidelines for economic evaluations and the manual for costing research [42, 43]. Out-of-pocket expenses will be valued using market prices derived from the tailored cost-questionnaire. Absenteeism at school (i.e., repeating classes, school drop-out) will be valued using the Dutch guidelines for intersectoral costs and benefits [44].

Stochastic and deterministic uncertainty in the CUA and CEA will be assessed by bootstrapping and sensitivity analyses respectively. Based on bootstrap analyses, cost-effectiveness acceptability curves will be constructed for a range of threshold values, the latter reflecting the maximum willingness to pay for an extra unit of effect. Sensitivity analyses will be conducted, e.g., for price estimates. Post-hoc subgroup cost-effectiveness analysis will be conducted, e.g., for adults and adolescents separately.

A MBEE will be conducted to explore the long-term cost-effectiveness of SNM for constipation, applying a life-long time horizon. Four types of data will be used as input for the model: probabilities, costs, survival, and utilities. The model input will be based on the trial results, results from the prospective cohort study, results from the formerly treated cohort in the participating centers, literature review, and expert opinion. Costs and effects will be discounted using discount rates of 4 and 1.5% respectively, corresponding to the Dutch guidelines for economic evaluations [42]. Probabilistic sensitivity analyses will be conducted to address uncertainty.

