### Randomization

After written informed consent, patients will be randomized according to the principle of minimization in a 3:2 ratio to SNM or PCT, using the online randomization database ALEA (ALEA software, TenALEA consortium, Amsterdam, the Netherlands), programmed by the Clinical Trial Center Maastricht (CTCM). Potentially confounding factors that will be used for minimization are study site, age, and gender. As SNM, a surgical intervention, is compared to conservative (medical) treatment, blinding to treatment allocation of patients and medical staff is not possible.

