## Discussion

More high-quality trials are needed to get better insight in the (cost-)effectiveness of SNM in slow-transit constipation since the current evidence shows conflicting results and is of suboptimal quality [15, 24, 25]. Our study contributes to this need and aims to assess the effectiveness and cost-effectiveness of SNM in patients with idiopathic slow-transit constipation refractory to conservative treatments. This study will be the largest to date with an intended inclusion of 64 adolescent and adult patients with slow-transit constipation. Previous published RCTs were small with respectively 2, 13, and 36 participants [20, 46, 47].

The No.2-trial differs from all four previously published crossover RCTs on SNM for constipation with regard to several aspects [20, 46–48]. First, our study will include both adolescents and adults with idiopathic slow-transit constipation while previous RCTs only included patients over 18 years of age. A prospective cohort study showed a 2-year SNM success rate of 42.9% in adolescents with idiopathic constipation [49]. From 2002 to 2015, adolescents were a substantial part (22.1%) of the population treated with SNM for constipation at the MUMC+. Since an effective therapy needs to be found for this specific population and as it is undesirable to exclude patients with school absenteeism up to 70% from treatment [50], our trial includes both adolescents and adult patients.

Second, our study specifically includes patients with idiopathic slow-transit constipation while most other RCTs included patients with various subtypes of chronic constipation [20, 46]. It has previously been shown that suprasensory SNM increases the pancolonic wave sequence in patients with slow-transit constipation which in turn corresponds to an increase in defection frequency [51, 52]. Therefore, our patient group will be more homogeneous compared to previous RCTs [20, 46].

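### Cost-effectiveness is to be analysed separately in adults and adolescents and labelled post hoc although the split is named in advance; separate ratios do not estimate whether cost-effectiveness differs by age

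*Protocol article*

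**What the plan says.** The Economic evaluation section plans a trial-based cost-utility analysis (cost per QALY, societal perspective) and cost-effectiveness analysis (cost per successfully treated patient, health care perspective), both over 6 months. Uncertainty is handled by bootstrapping, with acceptability curves over a range of threshold values. On subgroups it says only: "Post-hoc subgroup cost-effectiveness analysis will be conducted, e.g., for adults and adolescents separately". The article describes no estimate of the difference between the two age groups.

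The trial is sized on the overall primary endpoint, "with success rates of 35 and 5% for SNM and PCT respectively". The Sample size calculation section continues: "With a randomization ratio of 3:2, 38 patients will be randomized to SNM and 26 patients will be randomized to PCT". No expected number of adolescents is given. The nearest figure is historical and comes from the Discussion: "From 2002 to 2015, adolescents were a substantial part (22.1%) of the population treated with SNM for constipation at the MUMC". Under Randomization, age is one of the minimization factors: "Potentially confounding factors that will be used for minimization are study site, age, and gender".

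**The concern.** The sentence has two faults. First, it commits to an analysis and names the age split in advance, yet calls it post hoc. A reader of the results could not tell whether the split was foreseen or chosen after seeing the data.

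Second, the stated method is to run the analysis separately in each group. Each run answers what the cost per success or per QALY was in that group. Neither answers whether the groups differ, which is the only reason to split. Side by side, two ratios invite that comparison without supplying its estimate or its uncertainty. A ratio with a noisy difference in its denominator also moves a long way for small changes in counts.

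The results feed a national reimbursement decision, and the Discussion presents adolescents as a population that needs an effective therapy of its own. An adolescent ratio that looks much better or worse than the adult one could be read as a finding.

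**Working it through.** **Inputs.** From Sample size calculation: 64 patients, 38 SNM and 26 PCT, success 35% and 5%. From the Discussion: adolescent share 22.1%, used here as a proxy. Assumed: the same true success rates and the same fixed incremental cost ΔC in both age groups.

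**1. The plan's own figure.** With 36 + 24 = 60 evaluable patients, the exact power of the two-sided Fisher test is 81.0%. Allowing for 5% drop-out, 60 / 0.95 = 63.2, rounded up to 64. The stated size reproduces, for the overall comparison.

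**2. Subgroup sizes.** 0.221 × 64 = 14.1 adolescents: 0.221 × 38 = 8.4 on SNM and 0.221 × 26 = 5.7 on PCT. Take 8 and 6, leaving 30 and 20 adults. Age is a minimization factor, so a split near 3:2 within adolescents is reasonable.

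**3. Precision of the success difference.** SE = √(0.35 × 0.65 / n_SNM + 0.05 × 0.95 / n_PCT).
- Adolescents: √(0.2275/8 + 0.0475/6) = 0.191, so 0.30 ± 1.96 × 0.191 runs from −0.07 to 0.67.
- Adults: √(0.2275/30 + 0.0475/20) = 0.100.

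**4. Sensitivity of a ratio to one patient.** If adolescents show 2/8 against 0/6, the difference is 0.25 and the cost per success is ΔC / 0.25 = 4ΔC. With 1/8 against 0/6 it is ΔC / 0.125 = 8ΔC. One success doubles the ratio.

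**5. Chance divergence with no true difference.** With ΔC equal, the ratio of the two cost-per-success figures is the inverse ratio of the two success differences. Enumerating all binomial outcomes gives the following (a ratio is undefined when its success difference is zero or negative):

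| Adolescents (SNM/PCT) | Adults (SNM/PCT) | Both defined, at least twofold apart | At least one undefined | Total |
|---|---|---|---|---|
| 8/6 | 30/20 | 29.5% | 8.0% | 37.5% |
| 6/4 | 32/22 | 27.9% | 12.9% | 40.8% |
| 11/8 | 27/18 | 28.3% | 4.0% | 32.3% |
| 19/13 | 19/13 (even split) | 26.5% | 1.5% | 28.0% |

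The twofold column hardly moves with the adolescent share. What the small adolescent group mainly adds is undefined ratios.

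**6. Cost variation.** Fixed cost is the favourable case. With an assumed per-patient cost SD of 50% or 100% of ΔC, the total at 8/6 rises from about 37% to about 41% or 52%. The documents give no cost SD.

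**7. What the direct comparison would look like.** The difference between age groups in the success effect has SE √(0.191² + 0.100²) = 0.215 and 95% half-width 1.96 × 0.215 = 0.42.

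**The case against.** The best defence is that a post hoc label already tells readers to treat the result as exploratory, and that bootstrapping and acceptability curves, if applied within each age group, would display how uncertain each one is. Both points stand and limit the severity. Neither supplies the missing quantity: the spread of each group's bootstrap is not an interval for the difference between groups.

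Presenting results by age also has a rationale. The societal costs differ in kind, with patients' own productivity for adults, and parents' productivity and school absence for adolescents. That supports showing age-specific results, but not showing them without the comparison.

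The recommended estimate is itself imprecise, as step 7 shows. That is true and should be stated; an openly wide interval is less misleading than two ratios with no interval between them.

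Three stronger readings are tempting and not supported:
- A reader might infer that the small number of adolescents causes the twofold gaps. It does not, mainly: an even split gives nearly the same frequency. The figure of 14 is also only an inference from one centre's patients in 2002 to 2015, applied to a two-centre trial in which a paediatric referral centre is closely involved.
- A reader might fault the article for having no closed list of subgroups. A condensed article may leave that to the full protocol or analysis plan, so its absence alone is not an error.
- A reader might conclude that the cost-per-QALY ratios are equally unstable. That cannot be computed, because the article gives no SD for costs or QALYs.

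**Conclusion.** The point holds as a modest correction to a secondary analysis. The label contradicts a split announced in advance, and the separate-analysis method does not estimate a difference by age. With no true difference, the two cost-per-success ratios would be at least twofold apart in about 30% of trials, and at least one would be undefined in about a further 8%. This rests on success rates of 35% and 5% in both age groups, fixed incremental cost, and 8 SNM and 6 PCT adolescents. For adolescent numbers from 6/4 to 11/8 the combined figure runs from about 41% to 32%; for an even split it is about 28%. Ratio instability in a trial of 64 is the main cause. Severity is low to moderate. The sample size, the primary result and the overall ratios are untouched.

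**What to change.** Replace the subgroup sentence with wording to this effect:

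*Age group (14–17 against 18–80 years) is a pre-specified exploratory subgroup. The difference between age groups in incremental net monetary benefit (the arm-by-age-group interaction, estimated on all randomized patients) will be reported with its bootstrap 95% interval across the range of threshold values used for the acceptability curves. Age-specific ratios or curves will be shown only alongside this estimate, and no age-specific conclusion will be drawn from them alone. Any other subgroup analysis will be labelled post hoc.*

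Net monetary benefit is the threshold value times the incremental effect, minus the incremental cost. It stays defined when the effect difference is zero or negative. Using the threshold range already planned avoids having to choose a single willingness-to-pay value.

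The cost is one extra regression on data already collected, with no further patients or measurements. The interval will be wide: for success alone, the SE is about 21.5 percentage points and the 95% half-width about 42 points at the sizes used here. The plan should say so in advance.
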